### Sample Size Calculation and Statistical Analysis

Regarding the primary hypothesis and based on the published literature, we expect a rate of acute myocardial edema on T2 mapping in CMR in approximately 15% of patients with acute myocardial injury [17,36]. In the comparison groups with no or chronic myocardial injury, we expect a significantly lower rate (approximately 2%) presenting with acute myocardial edema [37].

To show a significant difference between the groups (two-sided α=.05), a sample size of 48 patients per group is required to reach a power of 80% and 89 patients per group for a power of 90%. Taking into consideration that in previous studies, due to impaired compliance or technical problems, the complete protocol of CMR could be realized only in approximately 85% of the study patients, we aim to include approximately 100-105 patients in each group.

Group comparisons (when comparing between the 3 groups) of the primary and secondary outcome measures (frequencies of specific alterations in CMR, TTE, and ECG) will be conducted using the chi-square test for categorical variables and, in case of continuous variables, using one-way analysis of variance or Kruskal-Wallis test, as appropriate. When comparing 2 groups (group 3 vs group 1 or group 3 vs group 2), Student *t* test will be used to compare continuous data. Logistic regression analyses will be used to calculate odds ratios and 95% CI to examine the association between elevated hs-cTn levels and the presence of specific structural and functional cardiac alterations in CMR and TTE. Multiple regression analyses using backward selection will be used to identify factors associated with certain myocardial alterations or ECG findings.

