## Methods

### Study Design

The CORONA-IS study is an investigator-initiated, prospective, observational, single-center cohort study that aims to include 300 patients with AIS. In November 2018, the Ethics Committee of the Charité-Universitätsmedizin Berlin, Germany (EA4/123/18), approved the study. All study procedures are carried out in accordance with the principles of Good Clinical Practice and the Declaration of Helsinki. The study was pre-registered under clinicaltrials.gov, NCT03892226. All patients with AIS admitted to the hospital within 48 hours of symptom onset are listed in a hospital-based registry as part of an assessment of high-sensitivity cTn (hs-cTn) development in patients with AIS. All study patients have to fulfill the study inclusion criteria listed in Textbox 1, and all participants have to provide written informed consent (for exclusion criteria refer to Textbox 2).

Inclusion criteria.ability to provide informed consentage ≥18 yearsdiagnosis of acute ischemic stroke and hospital admission within 48 hours of symptom onsetvisible diffusion-weighted imaging lesion in cerebral magnetic resonance imagingrepeated measurement of high-sensitivity cardiac troponin within 24 hours of admission

Exclusion criteria.pregnancy or breastfeedingimpaired renal function (estimated glomerular filtration rate <30 ml/min/1.73 m^2^)contraindications to undergo magnetic resonance imaging (eg, cardiac pacemaker, implantable cardioverter-defibrillator, and cerebral clips)persistent or permanent atrial fibrillation (patients with paroxysmal atrial fibrillation will be included if they are in sinus rhythm at admission or during cardiac monitoring of the stroke unit)ST-elevation in electrocardiogram fulfilling criteria of myocardial ischemiahistory of cardiac intervention (eg, coronary artery bypass surgery or percutaneous coronary intervention) within the last 4 weeks

Depending on serial measurements of hs-cTn during the acute hospital stay (assay characteristics: hs troponin T, Roche Elecsys, Gen 5; 99th percentile upper reference limit=14 ng/l; 10% coefficients of variation (CV) precision=13 ng/l; limit of detection=5 ng/l) and according to the fourth universal definition of MI, 3 groups are defined (Table 1) [4]. We aim to include 100 patients in each group. The cTn values are based on at least two blood exams: the first one at hospital admission and a control measurement within 24 hours after admission.

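### The two stated sample sizes, 48 per group for 80% power and 89 for 90%, cannot come from one calculation, and 48 does not give 80% in the equal-group comparison described

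*Protocol article*

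**What the plan says.** All the inputs are in the protocol article, Methods, Sample Size Calculation and Statistical Analysis.

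- Group 3 rate: "we expect a rate of acute myocardial edema on T2 mapping in CMR in approximately 15% of patients with acute myocardial injury".
- Groups 1 and 2 (no or chronic injury): "we expect a significantly lower rate (approximately 2%) presenting with acute myocardial edema".
- Error level: "To show a significant difference between the groups (two-sided α=.05").
- Result: "a sample size of 48 patients per group is required to reach a power of 80% and 89 patients per group" for 90%.

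The section then allows for complete cardiac MRI in only about 85% of patients and sets a target of roughly 100 to 105 per group. Study Design plans equal groups: "We aim to include 100 patients in each group".

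The three-group comparison of categorical outcomes uses the "chi-square test for categorical variables". Two-group comparisons appear in a sentence that goes on to the t test for continuous data: "When comparing 2 groups (group 3 vs group 1 or group 3 vs group 2"). The article does not say which contrast the sample size refers to or which formula was used, and it does not say that groups 1 and 2 were combined.

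**The concern.** Both figures are given in one sentence for the same rates and the same alpha, so one method should reproduce both. The gap between them is too wide for that. The lower figure also looks too small for 15% against 2% in equal groups.

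This is the only justification given for the size of the study, and edema is among the primary outcomes. Group 3 is the scarce group: the Background puts a rise/fall pattern at about 5% to 20% of stroke patients. If group 3 recruits slowly, a reader could take 48 evaluable patients as enough for 80% power. For a pairwise comparison it is not.

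**Working it through.** **Inputs.** p1 = 0.15, p2 = 0.02, difference 0.13, two-sided alpha 0.05 (z = 1.960), power 80% (z = 0.842) or 90% (z = 1.282), equal groups. All come from the two sections named above.

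**1. Attempt to reproduce 48 and 89: equal groups, pooled chi-square.**

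n = [1.960·√(2·p̄·(1−p̄)) + z_power·√(p1(1−p1) + p2(1−p2))]² / 0.13², with p̄ = 0.085.

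- First root: √(2 × 0.085 × 0.915) = 0.3944.
- Second root: √(0.1275 + 0.0196) = 0.3835.
- 80%: (0.7730 + 0.3228)² / 0.0169 = 71.1, so 72 per group.
- 90%: (0.7730 + 0.4915)² / 0.0169 = 94.6, so 95 per group.

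Neither stated figure is reproduced.

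**2. Other two-sided, equal-group methods.**

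| Method | n for 80% | n for 90% |
|---|---|---|
| Arcsine | 60 | 81 |
| Unpooled normal | 69 | 92 |
| Pooled normal | 72 | 95 |
| Continuity-corrected | 86 | 110 |

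Exact enumeration of the uncorrected Pearson test first reaches 80% at 63 per group. Fisher's test needs just under 80 (79% at 76, 82% at 80). None of these gives 48.

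**3. Power at the stated and expected sizes, equal groups.** Pooled power = Φ[(0.13·√n − 0.7730) / 0.3835]. At n = 48 this is Φ[(0.9007 − 0.7730) / 0.3835] = Φ(0.333) = 63%.

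| n per group | Pooled | Exact Pearson | Fisher |
|---|---|---|---|
| 48 | 63% | 72% | 48% |
| 85 | 87% | 91% | 85% |
| 89 | 88% | 92% | 87% |

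**4. Ratio check, which hardly depends on the formula.** In the simplest form, n is proportional to (z_alpha + z_power)². From 80% to 90% that gives (1.960 + 1.282)² / (1.960 + 0.842)² = 1.34. The pooled formula gives 94.6/71.1 = 1.33. The combined contrast in step 5 gives 66.4/47.6 = 1.40. The stated figures give 89/48 = 1.85.

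**5. Readings that might yield 48.**

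- *Group 3 against groups 1 and 2 combined (1:2).* p̄ = (0.15 + 2 × 0.02)/3 = 0.0633. The roots become √(1.5 × 0.0633 × 0.9367) = 0.2983 and √(0.1275 + 0.0196/2) = 0.3705. For 80%: (0.5847 + 0.3118)² / 0.0169 = 47.6, so 48 (48 against 96). For 90%: (0.5847 + 0.4749)² / 0.0169 = 66.4, so 67. With 89 in group 3, power would be 96%.
- *Three-group chi-square, 2 degrees of freedom.* It needs 51 for 80% and 67 for 90%. Power is 78% at 48 and 97% at 89 by the noncentral chi-square approximation, or about 75% and 96% by simulation.
- *One-sided arcsine, equal groups.* It gives 48 and 66, but contradicts the stated two-sided alpha.

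No variant tried gives both 48 and 89.

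**6. Which figure drives enrolment.** 89/0.85 = 104.7, so 105, the top of the stated target. By contrast, 48/0.85 = 56.5, so 57. The target therefore follows from 89.

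**The case against.** The best defence is that 48 may be correct for a contrast the article left unstated. One shared 2% rate is given for both comparison groups, which makes pooling them a natural reading, and 48 against 96 then gives 80% (pooled), 84% (exact Pearson) or 81% (Fisher). This stands as a possible origin of 48, so one cannot say that 48 is wrong under every contrast. It does not rescue the sentence, because the same contrast needs 67 for 90%.

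The figure 89 has a similar defence. Under exact Pearson power for a pairwise test it gives 92%, so the 90% claim can be met without moving to 95. That also stands, but by the same method 80% needs 63, not 48.

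Under the three-group chi-square, the shortfall at 48 is only about 2 to 5 points. The low pairwise power at 48 applies to pairwise tests, which the article names only in its sentence on continuous data.

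A reader might infer that the quoted power does not exist, or that the study is underpowered. The documents do not support either. Enrolment follows from 89, not 48, and nothing in the article makes 48 a stopping rule, a floor or a fallback. The abstract and the Results section speak of 300 patients with the complete MRI protocol. Read literally, that is 100 evaluable per group and about 92% pooled power.

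**Conclusion.** Wrong as written; moderate to minor in severity. The two figures are mutually inconsistent whichever contrast was meant. For two equal groups with 15% against 2% at two-sided 0.05, 48 per group falls short of 80% under every method tried: about 63% pooled, ranging from 48% (Fisher) to 72% (exact Pearson). The requirement is about 72, or 60 by the most lenient formula.

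The planned size is not in question for a single pairwise test. With 85% of 100 to 105 patients evaluable (85 to 89 per group), power is 87% to 88% pooled, and 85% to 92% across Fisher and exact Pearson. Only the conservative continuity-corrected formula, which needs 86 for 80%, is borderline at 85.

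This rests on the article's own rates, on equal evaluable groups, and on one test at 0.05. If alpha were split over two pairwise tests (0.025 each), pooled power at 85 to 89 would be 79% to 81%. The article does not propose such a split.

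**What to change.** State the contrast, the test and the formula, and derive both figures from that one calculation:

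- Pairwise, equal groups, pooled chi-square: 72 per group for 80% and 95 for 90%.
- Group 3 against groups 1 and 2 combined: 48 for 80% and 67 for 90%, saying explicitly that the comparison groups are pooled.
- Any other method is acceptable if it is named and both figures follow from it.

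Add the pairwise power at the expected 85 to 89 evaluable patients per group (about 87% to 88% pooled).

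The cost is one or two sentences. The enrolment target does not change and no extra patients are needed. If the pairwise pooled calculation is chosen, the power stated for 89 falls slightly, from 90% to about 88%.

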**Table 1 table1:** Definition of the 3 groups based on patients’ high-sensitivity cardiac troponin values.

Group	Description	hs-cTn^a^ values (URL^b^=14 ng/l)
Group 1	Normal hs-cTn levels	Both hs-cTn levels ≤URL
Group 2	Chronic myocardial injury (elevated but stable cTn levels)	At least one hs-cTn level >URL but *no* rise/fall (>20%) in serial measurements
Group 3	Acute myocardial injury (dynamic elevation)	At least one hs-cTn level >URL *and* rise/fall (>20%) in serial measurements^c^

^a^hs-cTn: high-sensitivity cardiac troponin.

^b^URL: upper reference limit (=14 ng/l).

^c^Or initial cTn value ≤URL and second value >URL+increase >50% URL (ie, 7 ng/l).

In addition to routine clinical procedures (refer to the *Baseline Visit* section), study patients receive a baseline assessment, an additional blood draw for biobanking, 3 Tesla (3T) cardiovascular magnetic resonance imaging (CMR), transthoracic echocardiography (TTE), and a 20-min high-resolution electrocardiogram (ECG) for a comprehensive assessment of cardiac autonomic function as well as a questionnaire testing cognitive function and the perception of stress. Furthermore, 3 and 12 months after discharge, patients will be followed up via structured telephone interviews for cardiovascular events and clinical outcomes (Figure 1).

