### Baseline Visit

The baseline assessment of the study patients includes demographics, medical history, medication, and information about the current stroke (time of symptom onset, time of hospital admission, and treatment including thrombolysis or thrombectomy). Stroke severity is classified using the National Institutes of Health Scale Score. The degree of disability is assessed using the modified Rankin Scale score. The presence of chest pain and dyspnea at admission and before the event is documented. Cognitive function and the individual perception of stress will be assessed via 2 questionnaires: Perceived Stress Scale and Montreal-Cognitive-Assessment [23,24]. In addition, the results of routine diagnostic procedures and stroke unit monitoring (eg, vital signs, 12-lead ECG, laboratory results, cerebral computed tomography imaging/MRI, and ultrasound of the brain-supplying arteries) are recorded.

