The second aim of the study is to investigate the role of CAN in the development of stroke-associated myocardial injury. There are different ways to display the influence of CAN on the cardiovascular system. Invasive diagnostic methods with direct recording of neural activity are not feasible in clinical settings. Noninvasive methods include for instance measurement of baroreceptor sensitivity or HRV. Reduced HRV and impaired baroreceptor sensitivity are associated with higher stroke severity and worse clinical outcomes [47,48]. However, these diagnostic tools represent only the combined sympathetic and parasympathetic influence on the cardiovascular system. There is evidence that increased sympathetic nervous activity can lead to destabilization of the myocardial repolarization phase [49]. In the CORONA-IS study, we will use the novel ECG markers, PRD, and DC*.* PRD assesses rhythmic modulations of cardiac repolarization in the low-frequency spectral range (≤0.1 Hz) [31,50]. Experimental and clinical evidence suggests that these low-frequency alterations are caused by phasic efferent sympathetic activity. DC is an integral measure of deceleration-related oscillations of the heart rate and primarily reflects parasympathetic activity [51]. PRD alone and in combination with DC have been shown to be a strong and independent predictor of sudden cardiac death in patients with MI [30,31,52]. To date, these markers have not been investigated in patients with AIS. They could provide important information regarding the assumed dysfunction of the CAN causing stroke-associated myocardial injury. It has to be kept in mind that these noninvasive measures can only serve to display an association between altered autonomic cardiac control and the presence of myocardial injury in stroke patients. To show a direct causation, further studies with nonobservational designs will be necessary. As the clinical differentiation between concomitant MI and stroke-associated myocardial injury is difficult, we aim to investigate whether specific biomarkers can help distinguish between both conditions. Therefore, we conduct thorough biobanking to evaluate the role of various potential biomarkers.

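### On the natural reading of the analysis section, the modified Rankin Scale at 3 and 12 months is compared across non-randomised troponin groups without adjustment for stroke severity or age

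*Protocol article*

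**What the plan says.** *Study Design* describes an "investigator-initiated, prospective, observational, single-center cohort study that aims to include 300 patients with AIS". Table 1 there gives the "Definition of the 3 groups based on patients’ high-sensitivity cardiac troponin values", and the target is stated as "We aim to include 100 patients in each group". Group membership is therefore observed, not allocated.

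Textbox 3 (*Study Outcomes*) lists four secondary outcomes: pathologic autonomic ECG markers (PRD and DC), high perceived stress, cardiovascular events at 3 and 12 months, and mRS at 3 and 12 months.

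*Sample Size Calculation and Statistical Analysis* contains three statements that matter here:

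- "Group comparisons (when comparing between the 3 groups) of the primary and secondary outcome measures" are to be made by chi-square for categorical variables and by one-way ANOVA or Kruskal-Wallis for continuous ones, with Student's t test for group 3 against group 1 or group 2. A parenthesis after the quoted words mentions only the frequency of CMR, TTE and ECG alterations.
- Logistic regression relates elevated troponin to "the presence of specific structural and functional cardiac alterations in CMR and TTE". No covariates are named.
- Multiple regression with backward selection looks for factors associated with myocardial changes or ECG results.

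*Baseline Visit* records demographics, and adds: "Stroke severity is classified using the National Institutes of Health Scale Score". It also says: "The degree of disability is assessed using the modified Rankin Scale score".

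**The concern.** None of the named group tests takes a covariate, and neither regression statement reaches mRS. Baseline NIHSS, mRS and age are recorded but have no stated role in the functional-outcome comparison.

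The article's own background makes confounding by severity plausible. The Discussion (*Overview*) says that cardiac complications are frequent in patients with acute, severe neurological events, which ties severity to the exposure. It also says: "Reduced HRV and impaired baroreceptor sensitivity are associated with higher stroke severity and worse clinical outcomes". The Introduction (*Background*) says that raised troponin goes with poor functional outcome. A crude mRS difference in the expected direction would thus appear to confirm the premise, even if group 3 simply had more severe strokes or older patients. The selection check in *Limitations* concerns exclusions for CMR contraindications, so it would not detect this.

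**Working it through.** **1. Does the group-comparison sentence cover mRS?** Its subject is the primary and secondary outcome measures. If the parenthesis were an exhaustive list, only the PRD/DC item of the four secondary outcomes would qualify. Perceived stress, cardiovascular events and mRS would fall out, leaving one item in four. Reading the parenthesis as illustrative fits the sentence better. On either reading, no stated analysis of mRS takes account of severity.

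**2. The plan's own figures.** There is none to reproduce for mRS. The only sample-size calculation concerns myocardial edema.

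**3. Size of the possible bias.** Inputs:

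- n = 100 per group: the target in *Study Design*.
- Two-sided alpha 0.05: the analysis section.
- True group effect: zero, by construction.
- Correlation ρ between baseline severity and outcome: assumed 0.3, 0.5 or 0.7.
- Severity imbalance d between two groups: assumed 0.2, 0.3 or 0.5 SD.

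Formulas (normal approximation, two groups):

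- Spurious difference = ρ × d, in SD units.
- Shift of the test statistic: δ = ρ × d × √(n/2) = ρ × d × √50 = 7.071 × ρ × d.
- Rejection probability = Φ(δ − 1.96) + Φ(−δ − 1.96).

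For ρ = 0.5:

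| d (SD) | spurious difference (SD) | δ | false-positive rate |
|---|---|---|---|
| 0.2 | 0.10 | 0.71 | 11% |
| 0.3 | 0.15 | 1.06 | 19% |
| 0.5 | 0.25 | 1.77 | 42% |

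Over the same range of d, the rate runs from 7% to 19% at ρ = 0.3 and from 17% to 70% at ρ = 0.7.

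**4. Check by simulation, three groups.** Binary poor outcome with logit = −1 + b × severity, 100 per group, no group effect, severity in group 3 shifted by d SD. The unadjusted chi-square used 2000 runs and the severity-adjusted likelihood-ratio test 500.

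| d (SD) | unadjusted, b = 1.0 | unadjusted, b = 1.5 | adjusted, b = 1.0 / 1.5 |
|---|---|---|---|
| 0 | 4% | 4% | 4% / 5% |
| 0.25 | 11% | 16% | 6% / 6% |
| 0.5 | 29% | 46% | 6% / 5% |
| 0.75 | 60% | 83% | 4% / 4% |

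**5. Check on a seven-level scale.** Here 400 runs were made with 100 per group, an assumed mRS distribution of 20/25/20/13/12/4/6% and latent correlation 0.5. At 0.3 SD imbalance the rank test rejected in 14%, chi-square in 10% and the adjusted ordinal model in 5%. At 0.5 SD the figures were 39%, 21% and 6%.

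The three calculations agree in direction and broadly in size. In both simulations the adjusted model contains the very severity variable that drives the outcome. NIHSS measures severity imperfectly, so real adjustment would reduce this bias without necessarily removing all of it.

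**The case against.** The strongest objection is consistency. The regression sentences are read strictly so as to exclude mRS, so the parenthesis in the group-comparison sentence should be read strictly too. The article would then assign no test to mRS, and what remains is an omission of the kind an article leaves to a full protocol or SAP. Part of this stands: a reader might infer that the article expressly prescribes unadjusted tests for mRS, and it does not. But the strict reading empties the phrase about secondary outcomes of three of its four items. The article also goes beyond silence, since it names tests for these outcomes and says where regression will be used.

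A reader might also infer that a group difference in mRS will be reported as an effect of myocardial injury. The text does not support that. The stated aims are mechanistic phenotyping, no hypothesis about mRS is given, and the Discussion concedes, for the autonomic measures, that only association can be shown.

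Nor does the article establish that a severity difference between groups is to be expected. Its sentence on autonomic markers concerns heart rate variability and baroreceptor sensitivity, not troponin groups, and no NIHSS by group appears. *Limitations* notes that the need for consent may underrepresent large infarctions and aphasia. That narrows the severity range and may weaken both the imbalance and the correlation.

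Baseline mRS is also a doubtful covariate as described. *Baseline Visit* does not say whether it is the pre-stroke value. The Figure 1 legend places that visit within 2 days of enrolment, whereas troponin is measured at admission and within the next 24 hours. It may therefore be a post-stroke value recorded after the exposure and overlapping with NIHSS. This objection stands and shapes the fix.

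**Conclusion.** The point holds in a limited form. On the natural reading, mRS at 3 and 12 months is compared across non-randomised groups without adjustment, although severity and age are recorded. Confounding by either is plausible from the article's own statements, and a crude difference could be mistaken for a consequence of myocardial injury.

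Its size is unknown. The range of 11% to 42% assumes 100 per group, no true effect, correlation 0.5 and an imbalance of 0.2 to 0.5 SD. Other assumed correlations widen it to 7% to 70%. These figures show how sensitive the unadjusted tests are; they do not predict this cohort's result. Because mRS is a secondary outcome in a mechanistic study, the change is advisable but does not affect the primary comparisons.

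**What to change.** In *Sample Size Calculation and Statistical Analysis*, state that mRS at 3 months and at 12 months will each be analysed by ordinal (proportional-odds) logistic regression on the three-level troponin group, with contrasts group 3 vs 1 and group 3 vs 2. Force in NIHSS and age, without backward selection, and say at which time point NIHSS is taken. Include baseline mRS only if it is the pre-stroke value, and say in *Baseline Visit* which it is. Report the unadjusted comparison alongside, labelled descriptive. If a full protocol or SAP already specifies such a model, a reference to it is enough.

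The cost is a sentence or two and one model per time point, with no new data and no effect on recruitment. There are two drawbacks. The proportional-odds assumption must be checked. And if myocardial injury worsens early stroke severity, adjusting for NIHSS removes that part of its effect, which is a further reason to show both results.

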### Study Outcomes

Our main hypothesis is that the development of stroke-associated myocardial injury in patients with AIS is based on a stroke-related interference in the CAN resulting in myocardial tissue alterations and dysfunction (ie, stroke-induced "myocardial stunning") [13]. Using a systemic and multimodal diagnostic approach, we aim to provide a detailed characterization of myocardial tissue, cardiac function, and autonomic cardiac regulation (Figure 3). Thus, outcome measures are primarily based on cardiac tissue characterization via CMR, functional assessment using TTE and CMR measurements, and values of specific autonomic ECG markers. Textbox 3 shows the detailed outcome measures. In summary, as we assume that patients with stroke-associated myocardial injury show a Takotsubo syndrome (TTS)/stress cardiomyopathy pattern of lesions in the myocardium, we will focus on the presence of wall motion abnormalities together with myocardial edema (T2 mapping) but without corresponding LGE in CMR [32,33]. Left ventricular dysfunction and wall motion abnormalities will be measured via cine imaging in CMR and TTE. As a correlate of chronic myocardial injury, we further assess myocardial fibrosis/scar via LGE, diffuse fibrosis via T1 mapping, and extracellular volume fraction (ECV%) [34]. To facilitate the differentiation between stroke-induced and coronary-mediated myocardial injury, we evaluate typical CMR signs suggesting a recent MI (ie, presence of co-occurring LGE and acute edema in CMR). Infarcted myocardium will be defined as a region with a mean signal intensity >5SDs relative to the remote uninjured myocardium on LGE images [35].

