Besides structural alterations of the myocardium, we further aim to clarify whether patients with AIS and stroke-associated myocardial injury show—especially transient—functional cardiac alterations. Cardiac dysfunctions, including wall motion abnormalities or reduced EF, are often seen in patients with ischemic stroke and other acute severe neurologic conditions [1,45,46]. Regarding our study population, we expect to see higher rates of changes in left ventricular systolic and diastolic functions in patients with dynamic troponin elevation.

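### The three-group chi-square named for the frequency outcomes does not target the primary edema hypothesis, because it cannot tell an excess in acute injury from an excess in chronic injury

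*Protocol article*

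**What the plan says.** All statements below are in the protocol article, under Sample Size Calculation and Statistical Analysis unless another place is named.

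- **Hypothesis.** For acute injury (group 3) the expected edema rate on T2 mapping is about 15%. Then: "In the comparison groups with no or chronic myocardial injury, we expect a significantly lower rate", put at about 2%. Group 3 is thus expected to exceed both other groups.
- **Function.** The Discussion (Overview) adds: "we expect to see higher rates of changes in left ventricular systolic and diastolic functions in patients with dynamic troponin elevation". It names no comparator.
- **Test for frequencies.** Comparisons across the three groups "of the primary and secondary outcome measures (frequencies of specific alterations in CMR, TTE, and ECG) will be conducted using the chi-square test". All six primary outcomes in the Study endpoints box are frequencies, two of them with an extent measure added.
- **Two-group comparisons.** "When comparing 2 groups (group 3 vs group 1 or group 3 vs group 2), Student *t* test will be used to compare continuous data". No two-group test is named for frequencies.
- **Logistic regression.** Its purpose is "to examine the association between elevated hs-cTn levels and the presence of specific structural and functional cardiac alterations in CMR and TTE". By Table 1, patients in groups 2 and 3 alike have at least one hs-cTn value above the upper reference limit.
- **Fibrosis.** Study Outcomes says: "As a correlate of chronic myocardial injury, we further assess myocardial fibrosis/scar via LGE". For this outcome it is chronic injury that is expected to stand out.

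**The concern.** The null hypothesis of the three-group chi-square is that all three rates are equal. It can be rejected because group 3 is high, because group 2 is high, or because both exceed group 1 by the same amount. Only the first of these is the stated edema hypothesis.

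The contrast of group 3 with group 2 is what separates acute injury from raised troponin in general, and it is the reason for enrolling a chronic-injury group. As worded, no analysis named for the frequency outcomes makes that contrast. A significant p-value for edema could then be reported without any test of whether acute injury differs from chronic injury.

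**Working it through.** **Inputs from the article.** Edema 15% in group 3 and 2% in groups 1 and 2; two-sided alpha 0.05; about 100 patients per group; complete CMR in about 85%. This gives 0.85 × 100 = 85 evaluable per group, or 0.85 × 105 = 89. The Results section speaks of 300 patients with complete CMR, so 100 per group is also shown.

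**The plan's own figures.** The article gives 48 per group for 80% power and 89 for 90%. For two groups with pooled variance, n = [1.960·√(2·p̄·q̄) + z·√(p₁q₁ + p₂q₂)]² / (p₁ − p₂)², with p̄ = 0.085, 2·p̄·q̄ = 0.1556 and p₁q₁ + p₂q₂ = 0.1275 + 0.0196 = 0.1471.

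- 80%: (1.960 × 0.3944 + 0.842 × 0.3835)² / 0.0169 ≈ 71.1, so 72.
- 90%: (1.960 × 0.3944 + 1.282 × 0.3835)² / 0.0169 ≈ 94.6, so 95.

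By this approximation 48 per group has 63.0% power and 89 has 88.1%. No single variant tried gives both 48 and 89, so the sample size does not show which comparison was meant to decide. What follows does not depend on it.

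**Hand example at 85 per group.** Take counts near the expected ones: 2 for a 2% rate and 13 for a 15% rate. With mean count e, X² = Σ(xᵢ − e)² / [e(1 − e/85)]; the 5% critical value on 2 df is 5.99.

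- Counts 2, 2, 13: e = 5.667; Σ = 13.44 + 13.44 + 53.78 = 80.67; X² = 80.67 / 5.289 = 15.25.
- Counts 2, 13, 2: the same three numbers reordered, so X² = 15.25 again.
- Counts 2, 13, 13: e = 9.333; Σ = 80.67; X² = 80.67 / 8.308 = 9.71.

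All three reject, but only the first is the stated hypothesis. The pairwise chi-square for 13 vs 2 is (11/85)² / (0.0882 × 0.9118 × 2/85) = 8.85, above 3.84. For 13 vs 13 it is 0. Requiring both contrasts therefore accepts the first pattern and refuses the other two.

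**Rejection rates.** These come from exact enumeration over binomial counts in three equal groups. The omnibus test is the Pearson chi-square on 2 df. *Both* means that group 3 is higher than group 1 and higher than group 2, each by a pairwise Pearson chi-square at two-sided 0.05.

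| Rates, groups 1/2/3 | Omnibus at 85 / 89 / 100 | Both at 85 / 89 / 100 |
|---|---|---|
| 2/2/15% (plan) | 95.1 / 95.8 / 97.5% | 85.0 / 87.2 / 91.7% |
| 2/15/2% (assumed) | 95.1 / 95.8 / 97.5% | 0.0 / 0.0 / 0.0% |
| 2/15/15% (assumed) | 91.7 / 93.2 / 96.1% | 2.5 / 2.4 / 2.5% |
| 2/10/2% (assumed) | 70.7 / 72.3 / 77.5% | 0.0 / 0.0 / 0.0% |

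The first two rows have identical omnibus columns because the statistic does not depend on which group carries which rate. Under 2/15/15% at 85 per group, group 3 vs group 1 alone is significant in 90.6%, so that contrast does not settle the question either.

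With Fisher's exact test (two-sided p ≤ 0.05, group 3 higher) in both contrasts, the same enumeration under 2/2/15% gives 77.8%, 80.7% and 86.4%.

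**The case against.** The best reply is that the article already foresees comparing group 3 with group 1 and with group 2. Moving from three groups to two forces a new test only for continuous data, since a chi-square applies unchanged to a 2×2 table. It can be taken to carry over, and an article may leave success criteria to the full protocol. This stands in part. The comparisons are foreseen and the remedy is short. But the article does not leave the test for frequencies open: it names one, ties it to the three-group comparison, and that test does not match the hypothesis stated just before it. The logistic model does not fill the gap.

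Four stronger readings are tempting, and the documents do not support them.

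- *A significant omnibus test, or group 3 vs group 1 alone, would count as success.* The article states no success rule. The word joining the two contrasts lists comparisons that may be made. One therefore cannot say that the plan would declare the hypothesis supported with group 3 equal to or below group 2.
- *The type I error is inflated many times.* Under 2/15/2% or 2/15/15% the omnibus null is false, so rejecting it is correct for that test. With all rates at 2%, simulation at 85 per group gives 3.9% rejections, below alpha. The fault is the target, not the size.
- *The risk follows from the plan's own rates.* It does not: with 2% in chronic injury, the true departure lies in group 3. The risk arises if that assumption fails.
- *Every frequency outcome is affected.* Fibrosis is expected to track chronic injury, so a three-group test suits it.

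Two further limits stand. The Discussion states the edema expectation only against normal troponin, so the claim of exceeding both groups rests on the sample-size section. And the Takotsubo pattern requires absence of late enhancement, so scar in group 2 could not by itself produce it.

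**Conclusion.** The point holds for edema, the outcome behind the sample size, and for the Takotsubo pattern, which contains edema. Left ventricular dysfunction is supportive only, since the article gives no rates and no comparator for it.

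The named test rejects as often when only chronic injury is high as when only acute injury is high (95% each at 85 per group), and in about 92% when the two are equally high. Requiring both contrasts succeeds in 85.0% under the planned rates and in about 2.5% when acute merely equals chronic. These figures assume equal groups of 85 to 100 evaluable patients. The 10% and 15% rates for chronic injury are illustrations.

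This is a mismatch between a named test and a stated hypothesis, worth correcting before analysis. It is not evidence that the plan would reach a false conclusion, because a careful reader would also look at the three proportions.

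**What to change.** In Sample Size Calculation and Statistical Analysis:

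1. For the frequencies of edema and of the Takotsubo pattern, name two planned contrasts, group 3 vs group 1 and group 3 vs group 2. Test each by chi-square or Fisher's test at two-sided 0.05, with the risk difference and its 95% CI.
2. Regard the primary hypothesis as supported only if group 3 is higher in both contrasts. Because both must be met, no alpha split between them is needed. This does not address multiplicity across outcomes.
3. Report the same two contrasts for left ventricular dysfunction as supportive.
4. In the logistic model, enter group (acute, chronic, none) in place of elevated hs-cTn.
5. Keep the three-group test as descriptive, and for outcomes such as fibrosis where chronic injury is expected to differ.
6. State the power for meeting both contrasts.

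**Cost.** Wording only, with no new data or patients. For edema under 2/2/15%, power falls from about 95–97% for the omnibus test to about 85% at 85 per group, 87% at 89 and 92% at 100 with chi-square contrasts. About 74 evaluable per group are needed for 80% and about 96 for 90%. Fisher's test costs several points more, so the choice should be fixed in advance. These figures do not carry over to the Takotsubo pattern, for which the article gives no rate.
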